**Assessment Criteria, Assessment Method and reporting of Safety, including Adverse Events**

Adverse events occurring during the clinical trial are followed up until the symptoms are resolved or stabilized. Adverse events that occur are coded using Preferred Terms (PTs) according to the Medical Dictionary for regulatory activities (MED-DRA). All adverse events (AEs) and serious adverse events (SAEs) that occurred after treatment and the unexpected adverse events (UAEs) related to the treatment in the trial are summarized according to the severity by the time point of onset using Preferred Terms (PTs) and prepared in graphs. These are recorded based on the self-report of the subjects and examination during their visits. In recording the AE-related information, the name and duration, the scope and severity of symptoms, the causal relation with the medical device, additional treatment, the outcome of AEs, and the status of seriousness are described in detail in the Special Form of the case report form (CRF).

Statistical analysis method: In this study, AEs indicate cases of new or worsened symptoms or signs that were not observed during the baseline assessment and include all signs, symptoms and diseases regardless of the causal relation with the medical device. In the event of AEs, the name of the related symptoms, time of onset, duration, severity of symptoms, and causal relation with the investigational device are recorded in CRF. The number of cases and the number of applicable subjects are calculated for each case of AEs, and the rate of occurrence of adverse events 95% two-sided confidence intervals are presented. The difference in the rate of AE occurrence between the two groups is compared using the chi-square test or Fisher's exact test.

Protocol Abstract(cont'd)

Estimated Accrual:

Target sample size 120 subjects (Study group 60 subjects, control group 60 subjects, including 20% drop-out rate)

Phase:

□ Phase I □ Phase IIa □ Phase IIb □ Phase III □ Phase IV □ Phase I/II ■ Other

Site of Study:

This protocol is performed as an:

■Inpatient ■Outpatient □Community □Ect. ( )

Length of Stay : (What is the length and frequency of hospitalization)

Follow-up will be performed on the day of surgery as well as 2 weeks, 3 months, 1 months and 1 year postoperatively.

Where will study be conducted:

□ Only at WMH □ Community ■ Multicenter ( ■Domestic □ Multinational)

Name of Sponsor / Funding Source:

Not applicable

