| Objectives:  **Primary objectives:** The study aims to **verify the equivalence of clinical outcomes** of endoscopic surgery to those of a conventional surgical technique for patients with lumbar spinal stenosis. In addition, the prospective clinical data of endoscopic surgeries will be analyzed to establish the **basis for clinical practice guidelines** and present a guideline for selection of treatment methods in clinical practice.  **Secondary objectives:** To this end, the **clinical efficacy and safety** of posterior decompressive laminectomy using the full-endoscopic uniportal technique will be compared with those of the conventional surgical method in patients with lumbar spinal stenosis at three study sites. | | | |
| **Rationale:**  According to the Health Insurance Review and Assessment Service (HIRA), the number of patients with spinal diseases, the target population of this study, was reported to be around 3.63 million in 2018 alone, showing an increase of 450,000 patients over the past five years. In particular, the number of patients with lumbar spinal stenosis (LSS) increased by approximately 32.4% in 5 years. According to the 2018 Statistical Yearbook of Surgery by the National Health Insurance, there were 7,218 cases of endoscopic spine surgery, an increase of 41.3% from 5,108 cases in the previous year, and the treatment cost also increased by 45.9%. Compared to the increase of 2.4% in the number of conventional spine surgeries from 165,573 cases to 169,706 cases for the same period, a significant increase is confirmed, indicating that the cases of endoscopic spine surgery show a trend of remarkable growth. In addition, the prevalence of spinal diseases is expected to gradually escalate with the increase in the senior population, and the burden of increased medical expenses for the treatment is also projected.  Posterior decompression in lumbar spinal stenosis and posterior lumbar discectomy in lumbar disc herniation are the most conventional methods used to resolve the patient's symptoms. | | | |

The conventional methods have problems in terms of much bleeding, postoperative pain, instability and a decrease of muscles around the spine, and therefore, minimally invasive surgery is performed to preserve anatomical structures. Unilateral laminectomy bilateral decompression (ULBD) is the representative, most commonly used minimally invasive technique, and other methods such as spinous process osteotomy and endoscopy are also used.

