It has been reported that minimally invasive surgery has a number of advantages compared to the conventional surgical technique, and the clinical outcomes are not different from those of the conventional open laminectomy. Recently, surgical techniques of spinal decompression and discectomy using endoscopy have been developed and applied in clinical practice. The endoscopic spine surgery is classified into uniportal endoscopic technique and biportal endoscopic technique depending on the number of ports for insertion of instruments. Since the surgical site is accessed through a skin incision of less than 1 cm, damage to the normal structure can be minimized, resulting in fewer postoperative complications such as pain and epidural adhesion.

However, although spinal surgeries **have been reported with good clinical outcomes in retrospective studies, clinical outcomes have not been confirmed in a multicenter, prospective, randomized clinical trial**. In addition, while the conventional open laminectomy and microscopic surgery currently performed on patients with lumbar spinal stenosis are covered by national health insurance and are appropriately applied for patients in need of surgical treatments, endoscopic spine surgeries are not fully accepted for health insurance coverage, and are performed only for limited number of patients with lumbar disc herniation. Most of the endoscopic sinal surgery studies reported in Korea are retrospective studies, and **only a handful of level 1 studies are available for establishing the efficacy and safety** of the endoscopic surgery compared to the conventional open laminectomy. Therefore, in this study, the efficacy and safety of endoscopic surgeries were compared with those of conventional open laminectomy with established clinical outcomes through a multicenter, prospective randomized trial.

Study design:

- Conduct a prospective, randomized study as a multicenter, assessor-blind, randomized, controlled, prospective clinical trial.
- The study will be conducted with the endoscopic group (Group 1) and conventional surgery group (Group 2) depending on the patient group assigned to the sub-study.

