# Patients with lumbar spinal stenosis who will undergo uniportal endoscopic decompressive laminectomy

- Target sample size: 120 subjects (Study group: 60 subjects, Control group: 60 subjects, including 20 % drop-out rate)
- Primary outcome: ODI (Oswestry disability index)
- According to a previous study [1], the MCID (Minimal clinical important difference) of ODI was 12.8 and in another previous study [3], the standard deviation of the ODI value at 1 year after decompressive laminectomy was 18.8. Assuming an equivalence limit of 12.8, under the conditions of alpha = 0.05, power = 0.90, two-sided 95% confidence interval, and follow-up loss at 20%, 60 participants are needed in each group.

[figure not shown]

Subject Recruitment Plan

This is a prospective, multicenter study which will recruit subjects at the Department of Neurosurgery of Seoul St. Mary’s Hospital, Chundam Woorideul Spine Hospital and the Wiltse Memorial Hospital (Anyang). Those who are planning to undergo one-segment or two-segment decompression surgery for lumbar spinal stenosis will be recruited as subjects and advertisement for subject recruitment will not be used.

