Statistical analysis method: Equivalency will be declared if the upper and lower limits of the 95% confidence interval (CI) of the treatment difference value of each group’s ODI score at 12 months postoperatively fall within the pre-defined equivalence margin (+-12.8).

1. Secondary Endpoints

The secondary endpoints for this trial include clinical outcomes (VAS, EQ5D-5L, ODI, walking distance and time, satisfaction after surgery, time required to return to daily activities postoperatively, POSAS), radiographic outcomes, and other surgery-related outcomes.

Statistical analysis method: For each group, the differences from the baseline values to the postoperative values and differences in the pattern of change between the two groups are analyzed using repeated measures analysis of variance (ANOVA). In addition, for specific within-group or between-group comparisons at each time point, the t-test is used, while applying the adjusted significance level considering the multiplicity of the test.

Satisfaction after surgery, time required to return to daily activities postoperatively, Patient and Observer Scar Assessment Scale(POSAS scale)

Statistical analysis method: The satisfaction after surgery, the time to return to daily activities postoperatively, and POSAS scale score at the time of final postoperative follow-up are comparatively analyzed between the two groups using the t-test.

- Radiographic outcomes

Examination of the occurrence of complications during the final follow-up using simple radiographs (Development of spondylolisthesis, progression of degenerative lumbar spinal conditions, etc.), analysis of surgical outcomes through postoperative MRI (or CT)

- Statistical analysis method: The occurrence of complications is examined for each group, and Chi- square test or t-test is used for comparative analysis on the difference between the two groups for the degree of central canal release and the canal dimension measured using postoperative MRI or CT.

- Other surgery-related outcomes

Comparison between the two groups on other surgery-related outcomes. [size of the surgical skin incision, postoperative drainage, operative time, duration of hospitalization (hours), Postoperative (From immediately after surgery to discharge from the hospital), postoperative Day 1 creatine kinase (CK, CPK)]

Statistical analysis method: The degree of difference between the two groups is evaluated using the chi-square test or t-test.

General Statistical Analysis

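### The between-group safety comparison is a chi-square or Fisher test with no clearly planned interval for the risk difference, so for uncommon events such as serious AEs or revision surgery the trial of 60 per group would not bound excess harm.

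*Protocol*

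**What the plan says.** Safety is part of the stated purpose. Under Objectives, the secondary objective is that the clinical efficacy and safety of the endoscopic technique "will be compared with those of the conventional surgical method in patients with lumbar spinal stenosis at three study sites". The Rationale adds that "only a handful of level 1 studies are available for establishing the efficacy and safety" of endoscopic surgery against open laminectomy. The primary objective also looks ahead to clinical practice guidelines.

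The method is in the section on assessment criteria and reporting of safety, under its statistical analysis method. AEs are defined broadly: they "include all signs, symptoms and diseases regardless of the causal relation with the medical device". Events and affected subjects are counted, and "the rate of occurrence of adverse events 95% two-sided confidence intervals are presented". Then: "The difference in the rate of AE occurrence between the two groups is compared using the chi-square test or Fisher's exact test". No target difference, margin or power is given for safety.

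The size of the trial is set under Statistical Consideration: "Target sample size: 120 subjects (Study group: 60 subjects, Control group: 60 subjects, including 20 % drop-out rate"). That figure is derived from the ODI margin of 12.8 and an SD of 18.8, and from nothing related to safety.

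**The concern.** For ODI, the protocol judges similarity from a confidence interval for the between-group difference, set against a margin. For safety it uses a test of no difference. Such a test can reveal an excess if it is large enough. When it is not significant, it does not say how large an excess is still compatible with the data. Only an interval for the difference says that, and none is clearly planned.

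This matters most for events that are uncommon but important, because there a trial sized on a continuous score is likely to return a non-significant result even when the true risk is materially higher in one arm. The result would stand beside an ODI equivalence statement in a report meant to inform guidelines, and the reader would have no stated limit on excess harm.

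**Working it through.** **Inputs from the protocol.** 60 per group, 1:1, 20% dropout included; ODI margin 12.8, SD 18.8, alpha 0.05, power 0.90. The safety set is everyone randomised and operated on, analysed by surgery received, so about 60 per group is the natural denominator.

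**Assumptions.** Two-sided alpha 0.05 for the safety test. Control event rates from 1% to 20%, because the protocol states none.

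**1. The plan's own figure.** For two one-sided tests with true difference zero, n = 2 × [SD × (z(1−α) + z(1−β/2)) / margin]². With α = 0.05 per side and β = 0.10: 2 × [18.8 × (1.645 + 1.645) / 12.8]² = 46.7, so 47 per group, and 47/0.8 gives 59. The t-based version needs 48, and 48/0.8 = 60. The 60 per group is therefore explained by ODI alone. (How this α relates to the 95% interval named for the ODI decision is a separate matter.)

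**2. Power of the planned safety test.** Exact power = Σᵢ Σⱼ Bin(i; 60, p_C) × Bin(j; 60, p_E) × 1[p-value(i, j) ≤ 0.05], over all 61 × 61 outcomes, with p_E = 3 × p_C. The miss rate is 1 − power; chi-square is uncorrected.

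| Control vs endoscopic | Missed, Fisher | Missed, chi-square |
|---|---|---|
| 1% vs 3% | 99% | 94% |
| 2% vs 6% | 94% | 82% |
| 3% vs 9% | 86% | 73% |
| 5% vs 15% | 67% | 54% |
| 6% vs 18% | 58% | 46% |
| 7% vs 21% | 49% | 39% |
| 10% vs 30% | 27% | 20% |
| 15% vs 45% | 6% | 4% |
| 20% vs 60% | 1% | <1% |

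A tripling is missed more than half the time up to a control rate of about 5% with either test (about 6% with Fisher). From about 7% both tests detect it more often than not. If only 48 per group contributed, 5% vs 15% would be missed 59% (chi-square) to 77% (Fisher) of the time.

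**3. Size needed for 80% power.** n = [1.960 × √(2p̄(1−p̄)) + 0.842 × √(p_C(1−p_C) + p_E(1−p_E))]² / (p_E − p_C)². This gives 141 per group at 5% vs 15%, 245 at 3% vs 9% and 62 at 10% vs 30%.

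**4. What a non-significant result leaves open.** Take 9/60 endoscopic and 3/60 open. The uncorrected chi-square is 0.10² / (0.10 × 0.90 × 2/60) = 3.33, p = 0.07; Fisher p = 0.13. The Wilson 95% limits are 0.081 to 0.261 for 9/60 and 0.017 to 0.137 for 3/60. Newcombe's interval for the difference is then:

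- lower: 0.10 − √[(0.150 − 0.081)² + (0.137 − 0.050)²] = −0.011
- upper: 0.10 + √[(0.261 − 0.150)² + (0.050 − 0.017)²] = 0.216

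The interval is −1 to +22 points. With 3/60 in each arm, p = 1 and the interval is ±√[(0.050 − 0.017)² + (0.137 − 0.050)²] = ±0.093, or ±9 points.

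**The case against.** The strongest reply is that this is a secondary, unpowered safety comparison, described in the ordinary way. Equivalence is formally claimed for ODI alone, and the safety objective is worded as a comparison. The planned counts and denominators would let anyone compute a risk difference later. The choice of interval method and the list of event categories could properly sit in an SAP that is not shown. Much of this stands, and it limits the weight of the point. It does not remove it, because the protocol does name the method for the between-group comparison, and the method named does not deliver a bound on the difference.

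Four stronger readings are tempting and are not supported.

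- A reader might infer that the test is the sole safety output. It is not: counts, intervals for AE rates, and summaries by severity and Preferred Term are planned. The interval sentence is also awkwardly worded, so the fair statement is that an interval for the difference is not clearly promised.
- A reader might infer that a tripling is missed more than half the time whatever the event. That fails from a control rate of about 7%. The test covers AEs of any cause, whose rate may well lie above that.
- A reader might infer that a non-significant test will be taken as equal safety. The protocol contains no such rule; it simply does not guard against that reading.
- A reader might infer that radiographic complications are also tested for significance. In the secondary-endpoint text they are examined by group, and the chi-square or t-test applies to canal release and canal dimension.

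**Conclusion.** The point holds in a limited form and is a cheap improvement to the plan, not an error that threatens its primary result. The stated between-group method cannot bound excess harm, although comparing safety with open surgery is a stated objective. For events with a control rate of about 5% or less, it has under 50% power against a threefold rise at 60 per group. Serious AEs, intervention-related complications and revision surgery are the likelier candidates, since each is a subset of all AEs and so can be no more frequent. For all-cause AEs the power may be adequate.

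The power figures depend wholly on assumed event rates. The absence of a clearly planned interval for the difference does not: the ±9-point width at 3/60 vs 3/60 shows that even identical observed counts leave a sizeable excess possible, and the planned test would not display it.

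**What to change.** In the statistical analysis method of the safety section, add as the main between-group safety result the risk difference (endoscopic minus open) with a two-sided 95% score-type interval, for example Newcombe's. Report it for any AE, serious AE, intervention-related complication and revision surgery, in the safety set. Keep the chi-square or Fisher test as a descriptive addition, and state that a non-significant test is not evidence of comparable safety. The safety statement should report the upper limit of the interval as the largest excess compatible with the data. No safety margin is needed for this, and the change adds no power.

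The cost is one or two sentences and a few lines of code on data already collected, best settled before results are seen. The downside is that the wide intervals will make the safety statement look visibly less favourable than a bare p-value.
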